**Figure 1 f1:**
[figure not shown]
A conceptual framework for the CarMeR Study.

This project, dubbed the Cardiometabolic Risks (CarMeR) Study, is by the Bill and Melinda Gates Foundation through the African Postdoctoral Initiative, managed by the African Academy of Sciences. The objectives are: 1. determine the prevalence of undiagnosed diabetes, prediabetes and other associated cardiovascular disease risks using the multi-sampled oral glucose tolerance test [OGTT] with 82.5g monohydrate dextrose, 2. characterize the phenotype of diabetes and prediabetes relative to body composition, body mass index (BMI), and other anthropometric measures, 3. establish the ocular characteristics and complications in people with diabetes and prediabetes, 4. ascertain whether the etiology of undiagnosed diabetes is predominantly insulin resistance or beta-cell insufficiency using homeostasis model analysis of beta [HOMA-β and HOMA-IR], 5. determine the sensitivity of diagnostic alternatives to the multi-sampled OGTT, specifically the fasting plasma glucose (FPG) test and the glycated hemoglobin (HbA1c) test, and 6. determine, over a 1-year period, if changes in food choices, physical activity, weight loss and psychosocial counseling influence reversal or prevention among people newly diagnosed with diabetes and prediabetes.

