### Population

The population comprises adults aged between 25 and 70 years living in households within the Cape Coast metropolis. The choice of this age range was influenced by the fact that they are at a higher risk of developing diabetes in the metropolis (41, 42). It is estimated that the number of people between the ages of 25 and 70 living in the Cape Coast Metropolis is 102,533 (43), spread across several households and communities in the metropolis. The sample for the study is being drawn from rural, peri-urban, and urban communities in the Cape Coast Metropolis. Owing to the heterogeneous nature of the Cape Coast population, the selection of participants for this study is based on different characteristics. These characteristics includes the type of community (rural, peri-urban, urban), main economic activity (farming, fishing, trading, formal work), dominant religion (Christianity, Islam, African traditional religion), and ethnicity (Fante, Ewe, Asante, northern tribes).

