### Participants

Following the protocol of the Research on Obesity and Diabetes among African Migrants (RODAM) study, which focused on obesity and type 2 diabetes among African migrants (44), this study estimates the prevalence of undiagnosed type 2 diabetes (T2D) in the Cape Coast metropolis of Ghana, at 6-7%, and the prevalence of obesity at 17%. The study aims for a power of 0.90 with α=0.05, including the Bonferroni correction. Using these parameters, a sample size of approximately 1000 would be sufficient to detect a 10% proportion of undiagnosed T2D. In order to compensate for attrition, the study seeks to recruit 1200 self-identified healthy individuals from 13 urban and rural communities in the Cape Coast Metropolis, who have not been previously diagnosed of diabetes or prediabetes prior to the study for collection of baseline data.

Due to the large and geographically dispersed population, a multistage sampling technique would be employed to sample participants for this study. This will be done in three stages, where the first stage involves dividing the population into clusters, based on the already existing communities within the metropolis. The second stage involves sampling these clusters to be used in the study by using systematic random sampling. At this stage, 13 clusters representing 13 rural, peri-urban and urban communities would be selected for the subsequent sampling stage. Finally, the third stage would involve further sampling within each selected cluster to randomly select households, and recruit the first two persons from each family line (with random replacement) in the indigenous communities, while using convenience sampling in non-indigenous communities. It is envisaged that approximately 90-100 participants will be randomly selected from three rural communities (Efutu Mampong, and Efutu), four fishing communities (Abekam, Duakor, Ekon, and Ntsen), three peri-urban communities (Ayeko-Ayeko, Ankaful and Nkanfoa) and one urban community (UCC), two market communities (Kotokuraba and Abura Markets), and one artisanal community (Siwdu). Household mapping will be done utilizing the 2021 Housing Census Data. All the 1200 volunteers will be recruited from their communities of origin before disclosing any monetary benefits.

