#### Inclusion criteria

Participants would be included in the study if they aged 25 to 70 years, and have not been diagnosed with prediabetes or diabetes. Additionally, participants should be willing to undergo the screening procedure (glucose testing, eye examination, BMI assessment, lipid level measurement, and body composition analysis). Participants diagnosed of diabetes based on a 2-hour OGTT glucose level between 11.1-17.0mml/L (200-300mg/dL) or prediabetes with 2-hour OGTT glucose level between 7.8-11.0 mmol/L (140-199mg/dL), would be followed up with a non-pharmacological lifestyle intervention for one year to assess the effect on their glucose tolerance.

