#### Exclusion criteria

Pregnant or breastfeeding women, individuals with pre-existing diabetes (either type 1 or type 2), those with a BMI below 18.5 kg/m², individuals with anemia, and those on cholesterol medications will be excluded from the CarMeR study. These exclusion criteria have been carefully selected to align with the study’s primary objective of ascertaining the prevalence of undiagnosed diabetes within a target population. Pregnant women are excluded due to the possibility of abnormal glucose tolerance precipitated by the pregnancy, and the return to normal glucose tolerance postpartum. Individuals with pre-existing diabetes are excluded to maintain the study’s focus on detecting previously undiagnosed cases, and the exclusion of participants taking high cholesterol medications is a measure taken to address the potential confounding impact of elevated cholesterol levels on diabetes prevalence. In addition, lactating mothers and individuals diagnosed with anemia are excluded because of the blood sample collection. Such participants may be at an increased risk of adverse effects or discomfort associated with the blood drawing process. The exclusion of these categories of people was intended to prioritize participant well-being, conform to the tenets of the Declaration of Helsinki for research on human subjects, and ensure the integrity of the study and the accuracy of its findings.

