#### Diagnoses

Diagnosis of abnormal glucose tolerance in the CarMeR study will be done using fasting plasma glucose (FPG), HbA1c and OGTT diagnostic tests based on the criteria suggested by the International Experts Committee Report on Diabetes and American Diabetes Association (59, 60). Participants are classified as having prediabetes if they have an FPG level between 5.6mmol/L and 6.9 mmol/L (100mg/dl and 125mg/dl), or an HbA1c level between 5.7% and 6.4% or a 2-hour OGTT result between 140mg/dl and 199mg/dl. Participants are classified as having diabetes if they have an FPG level of 7.0 mmol/L or higher (126mg/dl or higher), or HbA1c level of 6.5% or higher, or a 2-hour OGTT result of 200mg/dl or higher. Additionally, 1-hour post load plasma glucose (PG) will be used to diagnosed hyperglycemia (IH) and diabetes. Participant with a 1-h PG ≥ 155 mg/dL (8.6 mmol/L) are considered to have IH and should be prescribed lifestyle interventions and referred to a diabetes prevention program. Participants with a 1-h PG ≥ 209 mg/dL (11.6 mmol/L) will be considered to have diabetes. Generalized obesity is defined as body mass index (BMI) ≥30 kg/m^2^, and central obesity as a waist circumstance >102 cm in men or >88 cm in women, and a waist-to-hip (WHR of 0.88-0.89 (61, 62). Certified medical laboratory diagnostic scientists will perform all blood sample analysis at the Cardiometabolic Epidemiology Research Laboratory (CERL).

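### A past prediabetes diagnosis bars entry to the baseline survey, so such people who now have undetected diabetes are missing from the undiagnosed-diabetes prevalence

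*Protocol article*

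**What the plan says.** The Participants section seeks 1200 people "who have not been previously diagnosed of diabetes or prediabetes prior to the study for collection of baseline data". The Inclusion criteria agree: participants must "have not been diagnosed with prediabetes or diabetes". The bar therefore applies to the survey from which prevalence is estimated, and not only to the one-year lifestyle phase.

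The Exclusion criteria section says its exclusions were chosen to fit the "primary objective of ascertaining the prevalence of undiagnosed diabetes within a target population". Among prior glycaemic diagnoses it lists only pre-existing diabetes, of either type, and the reason given is to keep the "focus on detecting previously undiagnosed cases". No section gives a reason for barring past prediabetes.

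The Population section sets no limit on prediabetes history: "The population comprises adults aged between 25 and 70 years living in households within the Cape Coast metropolis". The Diagnoses section defines a case by current values: "Participants are classified as having diabetes if they have an FPG level of 7.0 mmol/L or higher", with alternative routes through HbA1c, 2-hour glucose and 1-hour glucose. Earlier prediabetes plays no part in that definition.

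**The concern.** The eligibility rule is narrower than the quantity to be estimated. A person who was once told of prediabetes, was never told of diabetes and now tests in the diabetes range meets the protocol's definition of diabetes and has not been diagnosed with it. That person belongs in the numerator of undiagnosed diabetes but is turned away before testing.

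At stake is the prevalence of undiagnosed diabetes, the quantity that the Exclusion criteria section calls primary. People with known prediabetes would be expected to have a higher diabetes rate than other adults, since the Introduction places prediabetes and diabetes on one continuum. Leaving them out would then pull the estimate down. A larger sample would not remove this, and the baseline data could not show how large it is.

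**Working it through.** The plan gives no figure for this loss. Its sample-size statement (about 1000, raised to 1200) does not depend on the point and does not change because of it.

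**Who is lost**

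| Person, never told of diabetes | Now in the diabetes range? | Undiagnosed case under Diagnoses? | Can enter the survey? |
|---|---|---|---|
| No past prediabetes diagnosis | Yes | Yes | Yes |
| Past prediabetes diagnosis | Yes | Yes | No |
| Past prediabetes diagnosis | No | No | No |

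The second row leaves the numerator. The second and third rows both leave the denominator, so the direction of the bias has to be worked out.

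**Formula.** Among adults without a diabetes diagnosis, let k be the share with a past prediabetes diagnosis, q the share of those now in the diabetes range, and p the prevalence in the rest. Then:

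- full prevalence T = (1 − k)p + kq
- prevalence that the restricted survey estimates = p
- shortfall = T − p = k(q − p)

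The shortfall is positive only if q exceeds p.

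**Inputs.** p = 6.5%, the middle of the 6–7% expected in Participants, taken here as the rate in eligible people (an assumption). The documents do not give k or q. The values below are assumptions.

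| k | q | T | Shortfall k(q − p) |
|---|---|---|---|
| 1% | 15% | 6.59% | 0.01 × 8.5 = 0.09 points |
| 2% | 15% | 6.67% | 0.02 × 8.5 = 0.17 points |
| 1% | 25% | 6.69% | 0.01 × 18.5 = 0.19 points |
| 2% | 25% | 6.87% | 0.02 × 18.5 = 0.37 points |

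Moving p to 6% or 7% barely matters: the smallest shortfall becomes 0.09 or 0.08 points and the largest 0.38 or 0.36.

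**Comparison with sampling error.** Under simple random sampling, the 95% half-width at N = 1200 is 1.96 × √(0.065 × 0.935 / 1200) = 1.39 points. Any clustering within the 13 communities would widen it. With q = 25%, the shortfall reaches this half-width only at k = 1.39/18.5 = 7.5%.

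**Direction.** If q were 5% with k = 2%, then k(q − p) = 0.02 × (−1.5) = −0.03 points, and the estimate would be slightly too high. That is unlikely, but the documents give no rate that excludes it.

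**The case against.** The strongest defence is that the bar belongs to a coherent design. Several sections can be read as seeking diabetes and prediabetes that are both undiagnosed (the description of the conceptual model in the Introduction and the opening of Methods). Participants asks for people who consider themselves healthy, and objective 6 concerns newly diagnosed people. On this view the study screens never-diagnosed adults for new dysglycaemia.

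Much of this stands, and it rules out several stronger readings that a reader might infer:

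- **That the eligibility sections contradict each other.** They do not. Inclusion and exclusion lists are cumulative, and an exclusion list need not repeat an inclusion criterion. What can be said is that the reason given for excluding known diabetes does not extend to past prediabetes.
- **That prediabetes prevalence is understated as well.** If undiagnosed qualifies prediabetes too, known prediabetes lies outside the target and nothing is lost there. The point is confined to diabetes.
- **That the bias is always downward.** It is downward only if q exceeds p.
- **That the shortfall could be 1.7 points, a fifth of the true value.** That needs k = 5% and q = 40% (0.05 × 33.5 = 1.7 points; T = 8.2%). The Introduction gives 6.5% diabetes prevalence in Ghana and 60% of cases undiagnosed in the Africa region. Roughly combined, diagnosed diabetes is 6.5% × 0.40 = 2.6% of adults. A k of 5% would mean about twice as many adults with known prediabetes as with known diabetes, and nothing in the documents supports that.
- **That the phenotype, ocular and test-sensitivity results are damaged.** At k = 2% and q = 25%, about 0.02 × 0.25 × 1200 = 6 cases are involved. No effect on those analyses can be shown.

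The defence does not remove the mismatch for diabetes. However prediabetes is read, a person with past prediabetes and undetected diabetes is an undiagnosed diabetes case. The interest in newly diagnosed people does not require the bar at baseline either, because entry to the one-year phase is decided after the baseline glucose test.

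**Conclusion.** The point holds as a mismatch between the baseline eligibility rule and the stated objective on undiagnosed diabetes. Its size is uncertain and probably small: about 0.1 to 0.4 points if k is 1–2% and q is 15–25%, which is below sampling error, and larger only if known prediabetes is common in the metropolis. The downward direction rests on the expectation that q exceeds p; the continuum described in the Introduction makes this plausible but supplies no rate. It is worth correcting because the correction is cheap and the enrolled data cannot reveal or repair the loss.

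**What to change.** Preferred change:

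- In Participants and Inclusion criteria, make known diabetes the only prior-diagnosis bar to the baseline survey.
- Clarify that the requirement to be self-identified as healthy does not exclude people with past prediabetes.
- Record past prediabetes as a questionnaire item.
- Count those now in the diabetes range, and never diagnosed with diabetes, as undiagnosed diabetes.
- Report undiagnosed prediabetes without previously known cases, or show the two separately.
- State the new-diagnosis condition for the one-year phase explicitly in the opening of Methods and in Inclusion criteria. At present the baseline bar supplies it, because Methods enrols all consenting participants found to have abnormal glucose tolerance. The wording should also say how a person with past prediabetes who is now in the diabetes range is handled.

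Minimum alternative: keep the bar, and restate the estimand as prevalence among adults with no previous diagnosis of diabetes or prediabetes, in the objectives and wherever the result is reported. This needs no change to eligibility.

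The preferred change costs an amendment, one questionnaire item, a flag in the prediabetes group and one extra entry line for the one-year phase. It adds no visits or tests and does not alter the sample size.

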### Questionnaire/survey questionnaire

The data collection consists of a survey questionnaire, anthropometric measurements, eye examination and collection of biochemical samples. The study will recruit volunteers from communities, markets, churches and schools in the 13 communities in rural, peri-urban and urban Cape Coast.

The WHO-STEPwise approach for identifying and explaining the risk factors for cardiometabolic diseases will be adapted in the data collection process of the CarMeR study. The WHO STEPwise questionnaire is adapted and modified to fit the Ghanaian NCDs context based on previous studies on NCDs in Ghana (45, 46). The first step involves gathering demographic and behavioral risk factor data using a questionnaire; the second step involves the collection of physical measurements; and the third step involves the collection of fasting blood samples for biochemical tests. In addition, the study will collect data on visual outcomes, including retinal changes, visual acuity, contrast sensitivity and visual field. The survey questionnaire consists of seven validated questionnaires that have been adapted to suit Ghanaian culture and the typical Ghanaian lifestyle. The survey questionnaire includes:

Perceived Stress Scale (PSS) (47): This questionnaire measures stress levels of participants in the past 1 month.Pittsburgh Sleep Quality Index (PSQI) (48): This questionnaire assesses sleep habits and quality of participants in the past 1 month.International Physical Activity Questionnaire (IPAQ) (49) assesses weekly physical activity levels of the participants.WHO STEPwise Inventory (40): This questionnaire assesses fruits and vegetable intake, smoking and alcohol consumption.Stunkard Figure Rating Scale (50): The Stunkard Figure Rating Scale assesses levels of body type satisfaction using a range of visual representations, starting from very slim (silhouette 1) to the point of significant obesity (silhouette 9).Visual Disability Questionnaire (51): This questionnaire assesses and quantifies the effects of visual impairment on daily activities.A validated questionnaire measuring neighborhood and environmental characteristics.

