### Enrollment visit

Prior to data collection, recruitment of participants is done by the research assistants (RAs). This is achieved through community engagement via the identified gatekeepers of the specific community. The gatekeepers subsequently organize their community members to engage with the research team. The RAs recruit eligible participants based on the inclusion criteria. The selected participants are assigned codes to anonymize them, and their contacts are collected. Participants who meet the inclusion criteria and agree to participate in the study are asked to sign an informed consent form. Prior to the day of the data collection, participants are called on phone and are reminded of the requirement to fast (8-12 hours), and not ingest any other fluid apart from water. Participants arrive at the study site at 6:30am as communicated to them, and they are asked to rest for a while before their vital signs were measured. Anthropometric measurements are taken, followed by baseline blood samples for FBG, creatinine, liver function tests (AST and ALT), and lipid profiles. After which, a three-point OGTT is performed to assess glucose tolerance. The whole and plasma blood samples are then sent to the CERL at University of Cape Coast, Ghana for analysis and preservation in a cryogenic freezer -40°C. The entire duration of the process is expected to last four hours. Subsequently, participants newly diagnosed with diabetes using a 2-hour glucose level between 11.1-17.0mmol/L (200-299mg/dL) are put into one cohort to complete 12 months lifestyle intervention program and monthly follow-ups. While participants identified with 2-hour glucose ≥ 17.0mmol/L (≥300mg/dL) are referred for medical treatment.

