### Data analysis

For the accuracy of data and information, data collected through the Kobo Collect toolbox application will be downloaded into an Excel spreadsheet and screened visually and statistically. Data will be analyzed and interpreted by the principal investigator and his local collaborators and shared back with foreign collaborators. In the attempt to make the findings of the study public, data analysis will be conducted using STATA 16 and SPSS 23. Statistical tools specific and relevant to the research questions and hypotheses of the CarMeR study would be used. To determine the prevalence of undiagnosed diabetes, prediabetes and other associated cardiovascular risks, data on OGTT, FPG and HbA1c will be analyzed using descriptive statistics (percentages and confidence intervals). In order to investigate the differences in phenotype, diabetes, prediabetes, and normoglycemic groups will be compared based on BMI and body composition (waist hip ratio, body fat percentage, skeletal muscle, total body water) using analysis of variance (ANOVA) and t-test. To profile the ocular characteristics and complications of the diabetes and prediabetes groups, a cross-tabulation and a subsequent chi-square test will be done to assess the association between glycemic dysregulation and the presence of ocular complications (diabetic retinopathy, cataract, macular edema). For the purpose of ascertaining whether the predominant etiological factor of undiagnosed diabetes in this populations is insulin resistance or beta-cell failure, a homeostasis model analysis of beta [HOMA-β and HOMA-IR] will be computed and logistic regression will be used to determine the dominant factor. As a way of determining the sensitivity of other diagnostic alternatives (FPG and HbA1c) in comparison to the multi-sampled OGTT, receiver-operated characteristics (ROC curves), including sensitivity and specificity curves, will be used. Finally, to ascertain whether lifestyle changes (food choice, physical activity, weight loss, psychosocial counseling) over a one-year period impacts biomarkers of glucose regulation, a linear mixed model regression analysis, controlled for baseline characteristics will be used. T-tests will be conducted to observe changes in glucose regulation biomarkers.

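### Convenience-sampled communities are described as randomly selected, and the recruitment sections do not tie enrolment to the sampled households

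*Protocol article*

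**What the plan says.** Under Population, the target is set as follows: "The population comprises adults aged between 25 and 70 years living in households within the Cape Coast metropolis". Prevalence of undiagnosed diabetes is the first listed objective, and Exclusion criteria calls it the primary one.

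Participants gives a three-stage design. Communities form the clusters. For choosing 13 of them, "The second stage involves sampling these clusters to be used in the study by using systematic random sampling". Within clusters, households are drawn at random and staff "recruit the first two persons from each family line (with random replacement) in the indigenous communities". The text then runs on, across two sentences: "while using convenience sampling in non-indigenous communities. It is envisaged that approximately 90-100 participants will be randomly selected from three rural communities". That second sentence applies random selection to the full list of rural, fishing, peri-urban, university, market and artisanal sites.

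Three later sections describe recruitment in other terms:

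- Data collection procedures has people aged 25 or over chosen at random within each household. It gives the gatekeepers' role as permission for community entry.
- Questionnaire/survey questionnaire: "The study will recruit volunteers from communities, markets, churches and schools in the 13 communities".
- Enrollment visit: "The gatekeepers subsequently organize their community members to engage with the research team", after which research assistants recruit those who meet the inclusion criteria.

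Data analysis plans percentages with confidence intervals for prevalence.

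**The concern.** A prevalence with a confidence interval supports a statement about a population only if people entered the sample by a known chance mechanism. Here one sentence prescribes convenience sampling for some communities and the next calls selection random in all of them. Unless every listed site is indigenous, which would leave the convenience clause with no use, both cannot be true.

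The operational sections add to the doubt. A field team working from Enrollment visit alone would find no instruction to go to a sampled household. Two rules for choosing people within a household also stand side by side: the first two per family line, and a random draw.

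Two conclusions are at stake. One is the prevalence for household residents of the metropolis. The other is any comparison by type of community, since Population names community type as a basis for selection and Expected outcomes lists location among the factors to explore. If convenience sampling falls on the market and university sites, a difference between them and the villages may be a difference in how people were found. This has to be settled before fieldwork, because no later analysis can recover selection probabilities that never existed.

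**Working it through.** **1. The plan's own figures.** Participants states about 1000 people to detect a 10% proportion, with power 0.90 and α = 0.05 with Bonferroni correction. A one-sample test of 7% against 10%, with two-sided α = 0.05/2 (two comparisons is my assumption), gives n = [2.241·√(0.07·0.93) + 1.282·√(0.10·0.90)]² / 0.03² = 1017. This agrees with the stated figure, which is not in dispute; the formula treats the sample as simple random. The community take also fits: 13 × 90 = 1170 and 13 × 100 = 1300 bracket the target of 1200, and 1200/13 = 92.3.

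**2. The statements side by side.**

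| Question | One statement | Another statement |
|---|---|---|
| Selection in non-indigenous communities | Convenience (Participants) | Random, for the whole list (Participants, next sentence) |
| Who is taken in a household | First two per family line (Participants) | Random draw (Data collection procedures) |
| How people reach the study | Random households from census mapping (Participants) | Volunteers at markets, churches and schools (Questionnaire); gatekeepers organise members (Enrollment visit) |

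The first row is a direct contradiction. The second is a difference in rule. The third is a gap: the later sections never refer back to the sampled households.

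**3. How far an overall figure could move.** The article does not say which communities are non-indigenous. Assume 3 or 4 of 13 (the university, the two markets and perhaps the artisanal site) with about equal numbers each:

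- Share of the sample: 3/13 = 0.231; 4/13 = 0.308.
- Shift in the overall percentage = share × bias at those sites.
- Bias of 1 point: 0.23 to 0.31 points. Bias of 3 points: 0.69 to 0.92 points.

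For scale, the nominal 95% half-width at 7% with n = 1200 is 1.96·√(0.07·0.93/1200) = 1.44 points. A shift that large would need a bias of 1.44/0.308 = 4.7 to 1.44/0.231 = 6.3 points at those sites.

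**4. Precision if the two parts are reported separately** (7% prevalence, same assumption):

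- Household-sampled: 1200 − 369 = 831 to 1200 − 277 = 923 people; half-width 1.74 to 1.65 points.
- Convenience-sampled: 277 to 369 people; nominal half-width 3.0 to 2.6 points. This is arithmetic only, since sampling error is not defined for such a sample.
- With clustering, at an assumed intracluster correlation of 0.01: design effect 1 + 91.3 × 0.01 = 1.91, and √1.91 = 1.38. The household-sampled half-width becomes about 2.3 to 2.4 points.

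**The case against.** The best defence is that much of this is condensed wording. Gatekeepers are elsewhere given the task of permitting entry, so Enrollment visit may describe mobilisation around household sampling. Participants calls all 1200 people volunteers, including those from sampled households, so that word need not mean a separate route. Churches and mosques are listed as places of data collection. These points stand. A reader might infer that sampled households would never be approached, but the text does not establish that; it only fails to exclude it.

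Four other inferences go further than the article:

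- **One unweighted, pooled percentage.** Data analysis mentions only percentages and confidence intervals. Weights and strata may be in an analysis plan that is not shown. Weights would not, however, supply selection probabilities for convenience recruits.
- **Similar numbers per community as a flaw.** The article does not say whether clusters are drawn with probability proportional to size. If they are, similar takes are roughly self-weighting, and census weights would count size twice.
- **Gatekeeper recruitment confounded with community type.** It is described as a general procedure. Only the random/convenience split could follow community type.
- **Reluctance to learn one's status, noted in the Discussion, as proof of bias in one route.** People in a sampled household can also refuse.

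The contradiction within Participants survives all of this. It could be argued that households are random everywhere and only the persons within them are taken by convenience. Even then the participants are not randomly selected.

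**Conclusion.** The point holds as a contradiction about how participants are selected and as a label that is untrue for part of the sample. Followed as written, the plan would report a partly non-probability sample as a random-sample prevalence for the household population, on the study's primary objective.

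Neither the size nor the direction of any bias can be determined from the article. The result of 0.2 to 0.3 points per point of bias rests on the assumed 3 or 4 sites and near-equal community sizes. A reader might conclude that the prevalence is shown to be seriously biased, but the documents do not support that: under these assumptions a 3-point bias shifts the figure by less than the nominal half-width.

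Nor would an estimate from the household-sampled communities alone be the metropolis prevalence. On the same assumption it leaves out both markets and the only community labelled urban.

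**What to change.** 1. In Participants, state the selection method for each community, and delete the words 'randomly selected' where convenience sampling is used.
2. Reconcile Data collection procedures, Questionnaire/survey questionnaire and Enrollment visit with Participants. In household-sampled communities, research assistants approach the sampled households, and gatekeepers only permit entry and mobilise. Keep one rule for choosing people within a household.
3. Record the recruitment route for each participant.
4. Report prevalence separately for the household-sampled and convenience-sampled communities, and label the latter non-probability. Do not describe any combined figure as a random-sample prevalence for the metropolis.
5. Describe the household-sampled estimate as covering those communities only. Match any weights to how the clusters were selected, and let the intervals allow for clustering.

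The cost is protocol wording, one recorded field and a split table; no site is dropped. The price in precision is a household-sampled half-width of about 1.6 to 1.7 points in place of 1.4 before clustering, and more with it. Refusals within sampled households would remain and should be reported.
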